#### Safety Measures and Reporting

For safety outcomes, we will include serious adverse events (SAEs), serious adverse reactions to trial treatments (SARs), and serious deteriorations (SDs). SAEs will be defined according to usual clinical trial definitions (ie, an event that is fatal, life-threatening, or results in or prolongs hospitalization; an increase in severe and persistent disability or incapacity; self-harm; or any other important condition that may require medical or surgical intervention to prevent the above [10] and will be reported to the appropriate authorities in the standard manner. SARs are SAEs that are considered to be a reaction to any trial therapy or drug prescribed. SDs will be defined as any of the following outcomes: CGI scores of 6 and 7, active withdrawal from the intervention due to worsening, or a reduction on the SF-36 PF scale by 10 or more points. Participants will record any nonserious adverse events (NSAEs) in their follow-up questionnaire. An adverse event is defined as any clinical change, disease, or disorder recorded by the participant, whether or not it is considered to be related to the trial or its treatments. Participants will be asked to record whether they believe the adverse event was “related to following the GET guide.” In the event of an adverse event (AE), the center leader will judge the seriousness of the event, and, if judged to be serious, the relationship to a trial supplementary therapy or SMC prescribed treatment, and the expectedness of the event. The trial manager will report all SAEs to the principal investigator (PI) within 24 hours, regardless of the relationship to trial treatment. Reporting of SAEs and SARs will be carried out according to normal regulatory research governance requirements.

After an SAE or SAR, the center leader will make a decision as to whether the participant should be withdrawn from either randomized treatment or from the trial, or if an alteration in their SMC is needed; arrangements will be made for further assessment and management as required. The trial manager will provide the center leader with monthly follow-up reports until resolution. These reports will be communicated to the Data Monitoring and Ethics Committee (DMEC), and other appropriate authorities via the trial manager.

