#### Non-Responders

If a returned form is incomplete, the researcher will contact the patient, usually by telephone, to acquire any missing data. In the event that no outcome data is completed or returned after 2 telephone attempts spaced 1 week apart, the researcher will email or text the participant to ask for answers over the telephone or via email solely for the 2 primary outcomes and the CGI. The researcher will make a file note that the outcome data were collected in this way. If a participant withdraws from the treatment, but not the trial, data will be collected in the usual way. If the participant is not willing to provide all follow-up data, a request will be made to complete only the primary outcome and CGI; if the participant agrees, these will be completed immediately.

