#### Missing Data

Item-level missing data on the primary and secondary outcome variables at baseline and follow-up will be imputed using mean replacement (prorating). Prorating will be implemented only when less than 20% of item responses per scale are missing. The reasons for missing baseline and follow-up whole-scale data will be summarized using the CONSORT diagram. We will identify baseline characteristics associated with missing data to allow us to impute data to do sensitivity analyses.

#### Analysis for Hypothesis 1

Our primary intention-to-treat analysis will compare the SF-36 PF and CFQ at 12 weeks between groups adjusted using multivariable linear regression analyses [45]. Intention-to-treat (ITT) analyses will be conducted on data from all randomized participants with information at follow-up (ie, modified ITT) regardless of any departure from the allocated treatment arm. We will adjust for our stratification factors (depression, center, and severity of disability) as well as baseline values of outcomes and treatment arm.

A secondary analysis will explore the association between treatment arm and having achieved a clinically useful improvement on the SF-36 PF (ie, an 8-point increase) and the CFQ (ie, a 3-point decrease) using chi-squared analysis.

Analysis of the secondary outcome, the CGI, will compare the proportions scoring “much” or “very much” better (1 and 2), the proportions scoring “a little better,” “no change,” or “a little worse” (3 to 5), and the proportions scoring “much” or “very much” worse (6 and 7) across treatment arms, using an ordinal logistic regression adjusting for our stratification variables.

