#### Sensitivity Analysis

Sensitivity analysis will be conducted to assess the impact of missing data on our results. We will estimate whole-scale missing data due to loss to follow-up using multiple imputation by chained equation. This will allow us to conduct a strict ITT for all respondents who took part at baseline. Following recent guidelines, we will also conduct a sensitivity analysis that will take into account the partially nested design of the study and, therefore, assess the potential impact of the “therapist effect” on our results [46]. Further analysis will be conducted to adjust for potential confounders, including sex and age.

A per-protocol analysis will serve as a further sensitivity analysis to investigate the robustness of the conclusions of the primary analysis, following departures from the randomized intervention policies. This will exclude those participants in the control arm who used a GET self-help approach. Subgroup analyses including only those meeting the Oxford or CDC criteria for CFS will also be undertaken. We will analyze moderators of improvement, such as these criteria, but also depression and severity of physical function and fatigue. These subgroup analyses are exploratory and will be interpreted with due caution [47].

#### Analysis for Hypotheses 2 and 3

Chi square will be used to describe any difference in satisfaction (ie, satisfied vs nonsatisfied) across treatment arms and any differences in SAEs, SARs, or serious deterioration (1+ vs none) across treatment arms.

The above plan is what we intend to do; however, the final analyses reported may differ from those planned, allowing for *post hoc* analysis where it is indicated [48]. We will report alternative methods if statistical models do not converge, and omit planned analyses that are superseded, redundant, or no longer of interest. We will report any changes in consequent papers.

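### After an SAE or SAR the center leader may withdraw a participant from the trial, not only from treatment, and nothing keeps outcome collection going, so the primary outcomes and some harm data can be lost selectively

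*Protocol article*

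**What the plan says.** The protocol article, under Safety Measures and Reporting, sets out what follows a serious adverse event or reaction: "the center leader will make a decision as to whether the participant should be withdrawn from either randomized treatment or from the trial". Treatment and trial are given as separate options. The same section has the event followed monthly until it resolves, with reports going to the DMEC. It defines serious deterioration by any of three components: a CGI rating of 6 or 7, active withdrawal because of worsening, or an SF-36 PF fall of at least 10 points.

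Under Non-Responders: "If a participant withdraws from the treatment, but not the trial, data will be collected in the usual way". A reduced data request is also described: "If the participant is not willing to provide all follow-up data, a request will be made to complete only the primary outcome and CGI".

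Under Analysis for Hypothesis 1, the primary comparison uses "all randomized participants with information at follow-up (ie, modified ITT) regardless of any departure from the allocated treatment arm". Under Sensitivity Analysis, whole-scale missing data are multiply imputed: "This will allow us to conduct a strict ITT for all respondents who took part at baseline". Under Analysis for Hypotheses 2 and 3, a chi-square test is planned for "any differences in SAEs, SARs, or serious deterioration (1+ vs none) across treatment arms".

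**The concern.** Read together, these sections let an investigator end a participant's outcome collection because a serious event has occurred. The missingness then depends on something that happened after randomization and that is probably related to the outcome. This differs from a participant who stops answering: the plan itself creates the gap, and it could be avoided.

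The stakes are highest for safety. Comparing serious events and serious deterioration between arms is the third stated hypothesis. The Introduction reports that patient surveys dispute the safety of graded exercise, and the Discussion makes release of the booklet conditional on GES proving acceptable and safe. Two of the three components of serious deterioration come from the follow-up questionnaires, so they cannot be scored once collection stops.

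**Working it through.** **1. What happens to a participant removed from the trial before 12 weeks**

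- *Continued collection.* The sentence on ordinary data collection covers people who leave treatment and remain in the trial. The reduced request depends on the participant's own unwillingness to give full data. Neither covers removal by the center leader, and no other section does.
- *Primary and main secondary outcomes.* With no 12-week SF-36 PF or CFQ, the participant falls outside the modified ITT set. With no CGI, they are also missing from the ordinal regression.
- *Sensitivity analysis.* The participant re-enters through multiple imputation. The Missing Data section plans to identify baseline characteristics associated with missingness for this purpose. A serious event after randomization is not a baseline characteristic, so the imputation is not designed to repair this kind of loss.
- *Triggering SAE or SAR.* This is not lost. It is already reported and followed to resolution, is reviewed under Independent Scrutiny, and counts as 1+ in the harm comparison.
- *Serious deterioration.* The CGI and SF-36 PF components may be missing. The third component is active withdrawal from the intervention due to worsening. Departure from Intended Treatment treats active withdrawal as something participants do, so removal by an investigator may not count.
- *Other harms.* Non-serious events are recorded by participants in the follow-up questionnaire and could be lost, as could SAEs after exit.

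The article does not say whether the harm comparison is one composite or three tests. In a composite, the triggering event already counts the participant. If serious deterioration is tested alone, the participant may be unscored or scored as none.

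**2. The plan's own sample size**

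Inputs from Sample Size: difference 8, SD 18, alpha 2.5% (two-sided fits), power 80%, loss 10%.

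- Normal approximation: n per arm = 2 × (2.2414 + 0.8416)² × 18² / 8² = 96.2, so 97. The two-sample t-test gives 97.5, so 98, as stated.
- Inflation: 98 / 0.90 = 108.9, so 109 per arm and 218 in total, as stated.

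**3. Effect on power (illustration)**

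With k further losses from one arm of 98: power = Φ(8 / [18 × √(1/98 + 1/(98 − k))] − 2.2414).

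| k | Power, SF-36 PF |
|---|---|
| 0 | 80.8% |
| 1 | 80.6% |
| 3 | 80.1% |
| 5 | 79.6% |
| 10 | 78.4% |

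Power barely changes. The issue is which participants are lost, not how many.

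**4. Effect on the arm mean (illustration)**

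If k of 98 are removed and their mean SF-36 PF differs by d points from those who remain, the observed arm mean shifts by (k/98) × d. Both k and d are assumed, because the article gives neither.

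| k | d = 10 | d = 20 | d = 30 |
|---|---|---|---|
| 1 | 0.10 | 0.20 | 0.31 |
| 3 | 0.31 | 0.61 | 0.92 |
| 5 | 0.51 | 1.02 | 1.53 |

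For 1 to 5 removals the shift is about 0.1 to 1.5 points, against the planned difference of 8. This is the shift in one arm; similar removals in both arms would partly cancel.

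**The case against.** The strongest objection is that the article describes a case-by-case decision, not a rule that data collection stops, and that the meaning of trial withdrawal for data retention commonly sits in the full protocol, which is not shown. That has some force: loss of the 12-week data is an inference. It is the natural one, though, because the article itself separates leaving treatment from leaving the trial and attaches continued collection only to the former.

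Four stronger readings are tempting, and the documents do not support them:

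- *That these participants leave the harm analyses.* They do not. The triggering event stays counted, and the restriction to those with follow-up information appears under Hypothesis 1, not under the harm analysis.
- *That the rule contradicts the intention-to-treat statement.* It does not. That statement concerns departures from allocated treatment among people who have follow-up information, and the plan openly calls the set modified ITT.
- *That follow-up is only by post, so leaving the trial can protect no one.* Non-Responders adds telephone, email and text contact, and the economic sections add clinic notes and databases. SAEs here include incapacity and self-harm, so some participants may be unable to take part.
- *That the loss favors GES.* Blinding to Outcome Measures names the TSC, DMEC and statistician as blinded and does not mention center leaders. The same leaders judge whether a serious event is related to a trial therapy, which is hard without knowing the arm. Even so, the article does not say whether they know allocation, so the direction of any bias is not established.

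It is also fair to object that follow-up has ended, so new questionnaires are no longer possible. This limits the remedy to reporting and analysis but does not make the stated rule sound.

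**Conclusion.** The point holds in a limited form. As written, an investigator may end trial participation after a serious event, no provision keeps outcomes coming in, and the primary analysis then omits that participant. What can be lost is the 12-week SF-36 PF, CFQ and CGI, two of the three components of serious deterioration, self-reported non-serious events and later SAEs. The triggering SAE or SAR is not lost.

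The size is unknown, since the article gives no SAE rate and no rate of withdrawal by center leaders. If serious events are few, the effect on the primary means is probably small, in line with the assumed 0.1 to 1.5 points above. No figure can be given for the harm contrast without inventing counts by arm. The conclusion assumes that withdrawal from the trial ends questionnaire collection, as the wording under Non-Responders implies. It is a cheap improvement worth making, not a threat to the main result.

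**What to change.** Leave the clinical decisions on randomized treatment and SMC as they are. Under Safety Measures and Reporting, add that a center leader's decision after an SAE or SAR does not end outcome and safety data collection. Collection continues by the routes under Non-Responders unless the participant withdraws consent or is unable to take part. State also that all randomized participants stay in their allocated arm for the primary, SAE/SAR and serious-deterioration comparisons.

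Because Results reports long-term follow-up complete in March 2016 with analysis under way, the practical step now is to report, by arm, how many participants a center leader withdrew from the trial. Keep them in the SAE/SAR and serious-deterioration denominators, and say how unscored components were handled.

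The cost is a sentence or two in the protocol and one line in the participant flow report, with no extra visits. The downside, for a trial still in follow-up, is that a few questionnaires go to people who are unwell, who can decline.

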#### Measures Used for Economic Evaluation

Quality of life and function will be measured using the EQ-5D and the WSAS. The EQ-5D will also be used to generate quality-adjusted life years (QALYs) and linked to costs measured using data collected with the CSRI. The IPAQ will determine PA participation before and after the intervention, and the TSK-F will determine beliefs about exercise at baseline. Participants will be asked about their current employment status and whether they have had to reduce/stop work due to their CFS/ME. The physiotherapist will record the number of contacts and the length of each contact, and during the final guidance session, will measure adherence to the GES guided support. Other service use during the trial will be reported by participants completing the CSRI at follow-up, including use of primary and secondary care services, use of other self-help approaches such as the Internet, books or voluntary sector support, medication, therapy outside of the trial, complementary healthcare, and care from family/friends. By accessing clinic notes and relevant electronic databases, we will also collect data on how many therapy sessions participants went on to receive after their trial participation up to one year after randomization.

#### Non-Responders

If a returned form is incomplete, the researcher will contact the patient, usually by telephone, to acquire any missing data. In the event that no outcome data is completed or returned after 2 telephone attempts spaced 1 week apart, the researcher will email or text the participant to ask for answers over the telephone or via email solely for the 2 primary outcomes and the CGI. The researcher will make a file note that the outcome data were collected in this way. If a participant withdraws from the treatment, but not the trial, data will be collected in the usual way. If the participant is not willing to provide all follow-up data, a request will be made to complete only the primary outcome and CGI; if the participant agrees, these will be completed immediately.

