### Interventions

#### Standard Medical Care (SMC)

Participants will be informed at the end of their assessment appointment that they have been allocated to SMC and that they should follow the advice of their GP and specialist doctor as usual. They will not have access to the self-help booklet used in the trial. As per usual, specialist doctors will prescribe or advise regarding medication as indicated for symptomatic treatment of associated symptoms (eg, insomnia and pain) and comorbid conditions (eg, depressive illness). These patients will start the therapy to which they have been referred after the endpoint of the trial at 12 weeks or more after randomization, when it becomes available. After completion of trial participation, these patients will also receive a copy of the GES booklet.

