#### 12-Weeks Post-randomization

The main outcome end-point will be 12 weeks after randomization, before patients begin their service therapy. We chose 12 weeks as this was about the length of the waiting list for therapy at the St Bartholomew’s CFS service at the time of application for funding. At the end-point, the following information will be collected via questionnaires sent by mail with a stamped addressed envelope: SF-36 PF, CFQ, self-rated Clinical Global Impression of Change (CGI) [39] (this will be done once for overall health and then a second time specifically for CFS), HADS, EQ-5D, WSAS, IPAQ, CSRI, and PHQ-15. Participants will be asked to describe the following: whether they have used any of 4 listed self-help resources since randomization, including the unpublished GES guide [40-42]; how satisfied they are with the help they received; how closely they followed the GES guide; their current employment status and whether they have had to reduce/stop work due to their CFS/ME; any new health problems not already reported; and whether they are taking antidepressant medication for any reason.

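### The rule that secures primary outcomes before service therapy stops at week 12, yet therapy can start and outcome collection can continue after that point

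*Protocol article*

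**What the plan says.** All references are to the protocol article.

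- **12-Weeks Post-randomization** states the intended order: "The main outcome end-point will be 12 weeks after randomization, before patients begin their service therapy". On collection it says: "At the end-point, the following information will be collected via questionnaires sent by mail with a stamped addressed envelope". On the choice of time point: "We chose 12 weeks as this was about the length of the waiting list for therapy", with the qualification that this was the St Bartholomew's service when funding was applied for.
- **Standard Medical Care (SMC)** says control participants start the therapy to which they were referred "after the endpoint of the trial at 12 weeks or more after randomization, when it becomes available".
- **Departure from Intended Treatment** requires follow-up measures to be completed before the therapy appointment when face-to-face therapy is offered before the 12 weeks are complete, and classes this as a protocol deviation.
- **Non-Responders** sets the chasing procedure: "In the event that no outcome data is completed or returned after 2 telephone attempts spaced 1 week apart", the researcher emails or texts to ask for answers "solely for the 2 primary outcomes and the CGI". A file note records that the data were collected in this way.
- **Analysis for Hypothesis 1** defines the primary analysis set as "data from all randomized participants with information at follow-up (ie, modified ITT) regardless of any departure from the allocated treatment arm".
- **Sensitivity Analysis** plans multiple imputation for missing whole scales. The one per-protocol exclusion it names is control participants who used a GET self-help approach.

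**The concern.** The trial compares GES plus SMC with SMC alone in people still waiting for therapist-delivered treatment. A primary outcome completed after that treatment has begun no longer measures this comparison cleanly. The investigators saw the risk, since they wrote a rule for therapy that arrives early. That rule stops at week 12, which is the point from which therapy may start in the ordinary course.

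After week 12, nothing in the article ties completion of the outcome to the first therapy appointment. The chasing procedure can still be producing primary outcome values then, and the analysis set accepts them without a condition on timing. At stake are some dilution of the treatment difference if both arms start therapy, and bias in either direction if late completion or uptake of therapy differs between arms.

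**Working it through.** **Timing, from the text**

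1. The earliest routine start of service therapy is week 12, depending on availability and not on return of the questionnaire. This is stated for the SMC arm; the article gives no separate start for the GES arm.
2. Collection is placed at the end-point, week 12. Non-response leads to two telephone attempts one week apart, then email or text. The article does not date the first call. If it is made at week 12, the second is at week 13 and the email or text request comes at week 13 or later.
3. The early-therapy rule applies only to offers before the 12 weeks are complete.

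Steps 1 and 2 can overlap from week 12 onward, and step 3 does not reach the overlap. The file note records how late data were obtained, not whether therapy had started. The named per-protocol exclusion does not remove such values.

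**The plan's own sample size**

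Inputs from Sample Size: SF-36 PF difference 8, SD 18; CFQ difference 3, SD 6; alpha 2.5%; power 80%; loss 10%. Sidedness is not stated; two-sided reproduces the figures.

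- SF-36 PF: n per group = 2(2.241 + 0.842)² × 18²/8² = 96.2, so 97. The t-test version gives 97.5, so 98, as stated. 98/0.9 = 108.9, so 109 per group and 218 in total, as stated.
- CFQ: the t-test version gives 77.3, so 78 per group. 78/0.9 = 86.7, so 87 per group and 174 in total, as stated.

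These figures stand and are not in question.

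**Illustration of the effect on power**

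Let p be the share of participants measured after therapy began, and L the fraction of the between-arm contrast lost in them. Neither is in the article; both are assumptions, with p taken as equal in the two arms and the SD held fixed.

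Diluted effect = planned effect × (1 − pL). Power = Φ(diluted effect/SE − 2.241), with SE = SD × √(2/98) = SD/7, so 2.571 for SF-36 PF and 0.857 for CFQ.

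| p | L | SF-36 PF effect | SF-36 PF power | CFQ power |
|---|---|---|---|---|
| 0 | – | 8.0 | 80.8% | 89.6% |
| 5% | half | 7.8 | 78.6% | 87.9% |
| 10% | half | 7.6 | 76.2% | 86.1% |
| 20% | half | 7.2 | 71.2% | 81.8% |
| 10% | all | 7.2 | 71.2% | 81.8% |
| 20% | all | 6.4 | 59.8% | 71.2% |

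For example, with p = 10% and L = half: 8 × (1 − 0.05) = 7.6; 7.6/2.571 − 2.241 = 0.714; Φ(0.714) = 76.2%.

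**A milder case built on the article's own figure**

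Sample Size cites an 11-point SF-36 PF rise over 12 weeks of practitioner-led GET. Assuming linear gain, two weeks of therapy is 11 × 2/12 = 1.83 points. If only controls gained this, the contrast lost is 1.83/8 = 23%. With 10% affected, the effect is 8 × (1 − 0.1 × 0.23) = 7.82 and power is about 79%. The 11 points are a change from baseline, not a gain over a control group, so this may overstate what therapy itself adds.

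**The case against.** The case for leaving the plan alone has several parts.

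- **The order is stated.** The article puts the end-point before service therapy, makes week 12 a floor for its start, and handles early offers. This is fair, but the statement is an intention attached to a nominal date, and no passage covers therapy offered from week 12 onward. The gap is real.
- **Posting dates and acceptance windows belong in the full protocol or SAP.** This stands. A reader might infer that the forms are posted only at week 12, but the text places collection there and gives no posting date. The missing posting date or cut-off is not a fault in itself. The point rests on an existing rule that stops short.
- **Therapy may rarely start so soon.** This largely stands. A reader might infer that appointments typically fall due at week 12. The 12-week wait was one centre's at the time of the funding application, no wait is given for Kent, and both the abstract's Conclusions and the Discussion speak of waits of many months. The share affected is probably small.
- **Chasing may be short.** A reader might put late values at weeks 14 to 16. The text fixes only one week between two calls, so about week 13 or later, given calls from week 12, is as far as it goes.
- **The direction of bias is not known.** This stands. A reader might infer that late values must pull the difference toward zero, or that GES participants reply faster. The article supports neither. GES contacts finish some 7 to 8 weeks after the first appointment and are with the physiotherapist, whereas the researcher chases the forms.
- **The larger power losses are implausible.** Affected participants must be both late and already in therapy, and a week or two of a treatment described as taking 3 to 6 months is unlikely to remove the whole contrast. This stands; the full-loss rows are outer limits.

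**Conclusion.** The point holds in a limited form. Followed as written, the plan can count primary outcomes measured after the start of therapist-delivered therapy as 12-week outcomes, because the rule that prevents this ends at week 12 while collection and therapy can both continue past it.

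The article gives no number of affected participants and no direction of bias. On assumed inputs, losing half the contrast in 10% of participants takes SF-36 PF power from about 81% to 76%; the milder two-week case leaves about 79%. CFQ has more room and keeps about 86% in the first case. The documents do not support saying that the primary comparison is invalid or that the sample size is wrong. The gap deserves correction because it touches both primary outcomes and can be checked cheaply.

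**What to change.** 1. Extend the rule in Departure from Intended Treatment so that the two primary outcomes and the CGI are requested before the first service-therapy appointment, whenever it falls. This changes when outcomes are requested, not when anyone's therapy starts.
2. Record the completion date of the primary outcomes and the date of the first therapy appointment. Measures Used for Economic Evaluation already provides for access to clinic notes and databases for therapy sessions up to one year.
3. Report by arm how many primary outcomes were completed after therapy began.
4. Add a sensitivity analysis that sets those values to missing and handles them under the multiple imputation already planned.
5. Reconcile the wording of the SMC, Departure from Intended Treatment, 12-Weeks Post-randomization and Non-Responders sections.

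The Results section reports that follow-up is complete and analysis is underway, so item 1 can only inform later use. The date comparison, the count by arm and the sensitivity analysis can still be done where dates are held. The cost is two recorded dates and one extra analysis. If no primary outcome proves to have been completed after therapy began, one sentence in the report settles the matter.
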